**Results:**

In this study, two comparative cohorts and an observational cohort will be set up. The primary outcome is the effect of emergency surgery, which is subject to assessment using the total mortality and comparison in the survival rate of SSICH patients on LOAPT between surgical treatment and conservative treatment. The second outcome is the safety of surgery, with the postoperative hemorrhagic complication which is compared between the operated SSICH patients on and not on LOAPT. Based on the observation of the characteristics and outcome of SSICH patients on LOAPT, the ischemic events after discontinuing LOAPT will be further addressed, and the coagulation function assessment system for operated SSICH patients on LOAPT will be established.

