### Outcomes and study endpoints

All patients will be closely monitored until death or 6 months after the occurrence primary hemorrhage. In this study, the following outcomes will be taken into consideration (Table 3). The primary outcome is the total mortality, including in-hospital and out-of-hospital mortality. The second outcome is the postoperative hemorrhagic complication, and the PIB is our main focus. The functional outcome of patients is another outcome interesting us and will be assessed using modified Rankin scale (mRS). The postoperative adverse cardiovascular/cerebral events (ACCE) include the region of original stroke enlarging, new ischemic stroke occurring outside the operative region, myocardial infarction, repeated revascularization, and deep venous thrombus. The screening, evaluation, and follow-up schedules are detailed in Table 4.

**Table 3 Tab3:** Outcomes to be taken in consideration

(1) Total mortality; (2) postoperative hemorrhagic complication; (3) patients’ functional outcome; (4) postoperative adverse cardiovascular/cerebral events (ACCE).

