## Results

China National Clinical Research Center for Neurological Diseases will be responsible for data analysis. Sample size was calculated by using PASS (Version 15, NCSS corporation, American). All sample size calculations were performed by conducting two-sided test, *α* = 0.05 and *β* = 80% (the degree of control = 80%). In this study, two comparison groups will be established, with the primary and secondary outcomes as the focus in this study. According to our unpublished data collected from 7 participating centers in 2019, for SSICH patients on LOAPT, the total mortality was about 30% for operated patients and 45% for the patients receiving conservative treatment, with the ratio of two groups reaching about 1:1.5. Moreover, for operated SSICH patients, the incidence of PIB was about 23% for patients on LOAPT and 10% for patient not on LOAPT, with the ratio of two groups reaching about 1:2.5. With regard to the primary outcome, our sample size was calculated as 196 (196 SSICH patients on LOAPT, operation group: *n* = 78; conservation group: *n* = 118). As for the secondary outcome, the sample size was 247 (247 operated SSICH patients, LOAPT group: *n* = 70; non-LOAPT group: *n* = 177). Moreover, in order to establish the coagulation function assessment system, the area under curve was expected to be 0.7, and the sample size was set to 92 (92 operated SSICH patients on LOAPT, PIB group: *n* = 23; non-PIB group: *n* = 69). In this case, a minimum of 387 SSICH patients (includes 118 patients on LOAPT receiving conservative treatment, 92 patients on LOAPT receiving emergency surgery, and 177 patients not on LOAPT receiving emergency surgery) may be required in this study to reach our research objective. Thus, to ensure final statistics, a total of 400 patients (patients on LOAPT receiving conservative treatment, *n* = 120; patients on LOAPT receiving emergency surgery, *n* = 100; patients not on LOAPT receiving emergency surgery, *n* = 180; Fig. 1) will be recruited. In this study, 10% of patients would be lost during follow-up. Finally, we decided to recruit 450 appropriate patients.

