All statistical analyses were conducted with the assistance of SPSS (Version 22.0, IBM, American). The data was indicated as mean (x) ± standard deviation (SD) for normally distributed data, median, and interquartile range (IQR) for skewed distributed data or number (*n*) and percentage (%). In this study, two main comparative groups and an observational cohort will be established, as shown in Fig. 1. Firstly, in order to investigate the effect of emergency neurosurgery, a comparison will be performed between SSICH patients on LOAPT receiving conservative treatment and those receiving emergency neurosurgery. Secondly, in order to investigate the safety of emergency neurosurgery, a comparison will be performed between operated SSICH patients on LOAPT and those not on LOAPT. Thirdly, in order to investigate the intra/postoperative complications and the risk of ischemic disease after discontinuing antiplatelet treatment, the characteristics of SSICH patients on LOAPT will be analyzed; moreover, because the history of previous neural ischemic events or cardiac events could affect the risk of postoperative ischemic events, we would perform the subgroup analysis depending on this history to further investigate the effect of discontinuing antiplatelet treatment on the risk of ischemic disease. The difference will be compared by conducting χ^2^ test, Mann-Whitney *U* tests, or Student’s *t* tests. The independent risk factors were analyzed by logistic regression, while the factors with *p* < 0.10 in univariate analysis were entered into a multivariate logistic regression model. The result was indicated as odd ratio (OR) and 95% confident interval (CI). The receiver operating characteristic (ROC) curve analysis was performed to test the prediction value of different parameters and different methods. An area under the curve (AUC) in a ROC analysis of ≥ 0.7 is considered as a clinical utility, while *p* value of < 0.05 was treated as statistically significant.

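### The plan expects 10% loss to follow-up, but names no method that can use a patient last seen alive before 6 months in the primary mortality comparison

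*Protocol article*

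**What the plan says.** **Outcome.** The protocol article's section Outcomes and study endpoints states: "The primary outcome is the total mortality, including in-hospital and out-of-hospital mortality". The Results paragraph of the abstract adds a "comparison in the survival rate of SSICH patients on LOAPT between surgical treatment and conservative treatment".

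**Follow-up.** The same outcomes section says: "All patients will be closely monitored until death or 6 months after the occurrence primary hemorrhage". Data collection has survival status recorded at the contacts 3 and 6 months after the hemorrhage.

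**Loss.** The sample size paragraph of the main Results section sets 400 patients as the number for the final statistics, assumes that "10% of patients would be lost during follow-up", and raises recruitment to 450.

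**Analysis.** The next paragraph of Results lists chi-square, Mann-Whitney U and Student's t tests for group differences. For modelling it says: "The independent risk factors were analyzed by logistic regression", with results given as odds ratios and 95% confidence intervals. ROC analysis is added for prediction. No Kaplan-Meier, log-rank or Cox method appears anywhere in the article.

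**The concern.** Chi-square and logistic regression need to know, for every patient, whether he or she was dead or alive at 6 months. A patient last seen alive at 3 months has no such value. Either the patient leaves the analysis or someone assigns a status.

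Exclusion is not neutral. Observed deaths all stay in the numerator, while patients alive at last contact leave the denominator. Unless the lost patients go on to die at their group's full average rate or more, each group's mortality is overstated. If loss differs between operated and conservatively treated patients, the treatment comparison shifts as well. Treatment is not randomised (Study design; Ethics and public involvement), so equal loss cannot be taken for granted. Exclusion also discards the follow-up these patients did contribute.

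**Working it through.** **Inputs.** From the sample size paragraph: mortality 30% operated and 45% conservative, and 10% loss overall. Unequal loss of 5%/15% and 15%/5% (operated/conservative) is assumed here for illustration; the article gives no loss by group.

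**The plan's own loss adjustment.** 400 / 0.90 = 444.4, so 445. The stated 450 leaves 450 × 0.90 = 405. The inflation is adequate, and it is the usual adjustment when lost patients do not count in the analysis.

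**Planned effect without loss.** Difference 45 − 30 = 15 points. Risk ratio 0.30 / 0.45 = 0.667. Odds ratio (0.30/0.70) / (0.45/0.55) = 0.524.

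**Completers-only mortality.** Let p be true 6-month mortality, l the fraction lost, and m the risk of death by 6 months in lost patients relative to their group average. Then

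completers-only mortality = p(1 − l·m) / (1 − l).

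With m = 0 (no lost patient later dies) this is p / (1 − l). With m = 1 (full average risk) it is p.

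Results for m = 0:

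| Loss, operated / conservative | Operated | Conservative | Difference | Odds ratio |
|---|---|---|---|---|
| 10% / 10% | 0.30/0.90 = 33.3% | 0.45/0.90 = 50.0% | 16.7 | (0.30/0.60)/(0.45/0.45) = 0.500 |
| 5% / 15% (assumed) | 0.30/0.95 = 31.6% | 0.45/0.85 = 52.9% | 21.4 | (0.30/0.65)/(0.45/0.40) = 0.410 |
| 15% / 5% (assumed) | 0.30/0.85 = 35.3% | 0.45/0.95 = 47.4% | 12.1 | (0.30/0.55)/(0.45/0.50) = 0.606 |

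With m = 0.5 the three differences are 15.8, 18.2 and 13.5 points. With m = 1 all return to 15.0. With equal 10% loss the risk ratio stays at 0.667 throughout.

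**Assigning a status instead.** Counting every lost patient as alive gives p(1 − l·m). This is correct when m = 0. At m = 1 and 10% loss it gives 0.30 × 0.90 = 27.0% and 0.45 × 0.90 = 40.5%, a difference of 13.5 points. Neither simple rule is safe.

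**Simulation of the alternative.** One million patients per group were simulated with true mortality 30% and 45%. By assumption, 60% or 80% of deaths fell in the first 30 days, and loss occurred only among patients alive after day 30, independently of later death.

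| Loss | Completers-only difference | Kaplan-Meier difference |
|---|---|---|
| 10% / 10% | 16.0 to 16.2 | 15.0 |
| 5% / 15% | 19.5 to 20.3 | 15.0 to 15.2 |
| 15% / 5% | 12.3 to 12.7 | 14.9 to 15.0 |

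Kaplan-Meier recovers the truth because non-informative censoring is built into the simulation. The exercise shows what is gained when that assumption holds, not that it does hold.

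**The case against.** **No contradiction.** A reader might infer that the abstract promises a time-to-event analysis that the methods then fail to deliver. The article does not support this. Survival rate can mean the proportion alive at 6 months, the outcomes section defines mortality over a horizon common to all patients, and the sample size rests on two proportions. With complete vital status, chi-square and logistic regression would be legitimate. This stands.

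**Exclusion is not stated.** A reader might also infer that lost patients are dropped and that the primary result is therefore distorted. The article never says what happens to them, and the inflation to 450 only suggests exclusion. The rule could be in a fuller plan that is not shown, and its absence here is no fault. What remains is that the methods the article does name cannot use partial follow-up, while the article itself expects 10% loss.

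**The size is conditional.** The formula deaths / (1 − loss) requires that no lost patient dies before 6 months. Being alive at last contact is not the same as being alive at 6 months. At the stated 10%, if equal between groups, the difference moves by at most 1.7 points. If the same fraction of survivors is lost in each group and no one else, the odds ratio does not move at all. The larger shifts rest wholly on the assumed splits. All this stands. The article also gives no timing of deaths or losses, so it cannot be said how much of the risk period lost patients would have been observed for.

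**The quoted sentence concerns risk factors.** True: the main comparison rests on the list of tests beside it. None of those handles censoring either.

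**The remedy has its own assumptions.** Non-informative censoring cannot be tested from the data, and a Cox model adds proportional hazards, which may fail for surgery against conservative care. This is why the fix relies on the 6-month risk difference and keeps the binary analysis alongside.

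**Conclusion.** The point holds in limited form. The plan expects loss to follow-up but names only methods that need known 6-month status, so patients last seen alive earlier must be excluded or assigned a status. If they are excluded, 10% loss in each group gives mortality of 30.0-33.3% and 45.0-50.0%, a difference of 15.0 to 16.7 points and an odds ratio of 0.524 down to 0.500. The unchanged ends assume that lost patients carry their group's full average risk, and the others that none of them later dies. If lost patients were at higher than average risk, exclusion would understate mortality instead.

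Material bias in the comparison needs unequal loss, for which the article gives no figure; the 12.1- and 21.4-point differences illustrate what such loss could do and are not forecasts. The point is an inexpensive improvement that should be made. It does not show that the primary result will be wrong.

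**What to change.** - **Primary comparison.** Estimate 6-month mortality in each group by Kaplan-Meier, censoring at last contact, and report the risk difference with a 95% confidence interval.
- **Adjusted effect.** Use a Cox model with confounders specified in advance (the article does not list any). If hazards are not proportional, rely on the 6-month risk difference.
- **Sensitivity analysis.** Keep the chi-square and logistic analysis, with a written rule for patients whose 6-month status is unknown.
- **Data.** Record the date of death and the date of last contact on the case report form. The article mentions survival status at 3 and 6 months but not these dates; the schedule table that might show them is not available here.

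Recruitment and planned contacts are unchanged. The cost is analysis work and wording, plus the two dates if they are not already collected. The downside is the reliance on non-informative censoring, so the number of patients lost and the time of loss should be reported by group.

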**Methods:**

As a multicenter and prospective cohort study, it will be conducted across 7 representative clinical centers. Starting in September 2019, the observation is scheduled to be completed by December 2022, with a total of 450 SSICH patients recruited. The information on clinical, radiological, and laboratory practices will be recorded objectively. All of the patients will be monitored until death or 6 months after the occurrence of primary hemorrhage.

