## Methods

### Study design

Surgical treatment for antiplatelet intracerebral hemorrhage (SAP-ICH) is an ongoing and multicenter study; the flow chart of which is shown in Fig. 1. Beginning in September 2019, this trial is scheduled to be completed by December 2022. Due to unknown and hugely potential intracranial hemorrhage complications after neurosurgery, ethical issues need to be taken into account; therefore, the randomized controlled trial was not suitable currently. The purpose of this study is to evaluate the effect and safety of emergency surgery for SSICH patients on LOAPT, with the focus placed on four aspects: (1) the outcome of operated SSICH patients on LOAPT; (2) the risk of intraoperative and postoperative hemorrhagic complications; (3) the risk of developing postoperative ischemic diseases for SSICH patients on LOAPT; (4) the methods to assess the coagulation state of operated SSICH patients on LOAPT.

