### Ethics and public involvement

Patients or the public were not directly involved in design or conduct of the study. This study was granted approval from Institutional Review Board of Beijing Tiantan Hospital, and the research would be conducted in strict accordance with the declaration of Helsinki and Human Biomedical Research Ethical Issues. In this study, researchers are not able to use randomized controlled trials; thus, all recruited SSICH patients will not be affected by normal course of diagnosis and treatment. When SSICH patients are included, they will be followed up until 6 months after the occurrence of primary hemorrhage.

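### The surgery comparison in a non-randomised cohort is fixed on unadjusted tests plus a p < 0.10 screened risk-factor model, so no reliable adjusted surgery effect on mortality is guaranteed

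*Protocol article*

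**What the plan says.** The Abstract describes the design: "As a multicenter and prospective cohort study, it will be conducted across 7 representative clinical centers". Study design says that "the randomized controlled trial was not suitable currently", and Ethics and public involvement says that "all recruited SSICH patients will not be affected by normal course of diagnosis and treatment". Whether a patient is operated on is therefore settled in ordinary care.

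Under Outcomes and study endpoints, "The primary outcome is the total mortality, including in-hospital and out-of-hospital mortality". The statistical paragraph in Results says that, to study the effect of surgery, "a comparison will be performed between SSICH patients on LOAPT receiving conservative treatment and those receiving emergency neurosurgery". It then names the methods for all group comparisons in one sentence: "The difference will be compared by conducting" a χ² "test, Mann-Whitney *U* tests, or Student’s *t* tests". Only the χ² test suits a yes/no outcome such as death.

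The only multivariable method is a logistic regression for independent risk factors. Factors with p < 0.10 "in univariate analysis were entered into a multivariate logistic regression model", with results given as odds ratios and 95% intervals. No confounder is named, no term is kept in regardless of p, and no weighting or matching is described. Prior ischaemic or cardiac history is recognised as affecting an outcome, but it is handled by subgroup analysis and only for ischaemic events.

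**The concern.** The study wants the effect of surgery on death, as a basis for choosing treatment. Without randomisation, factors such as age, GCS, haematoma volume and site, intraventricular blood and centre may influence both who is operated on and who dies. An unadjusted test mixes that selection with the effect of surgery, in either direction.

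The regression does not repair this. If treatment is screened like any other factor, an adjusted surgery effect exists only when the crude one is already close to significance. If treatment is not in the model, the regression does not address the primary question. In both cases a real confounder that misses p < 0.10 at this sample size is left out. The same structure applies to postoperative intracranial bleeding (PIB) in operated patients on versus not on LOAPT.

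**Working it through.** **Inputs from the article (Results, sample-size paragraph).** Mortality 30% operated and 45% conservative; ratio 1:1.5; primary sample size 78 + 118 = 196; recruitment target for these two groups 100 and 120; two-sided α 0.05; power 80%. Crude odds ratio: (0.30/0.70)/(0.45/0.55) = 0.524.

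**The plan's own figure.** The usual pooled two-sided formula gives 137 + 206 = 343 for these inputs, not 196. That is a separate matter; 78/118 and 100/120 serve here only as group sizes.

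**Step 1. How often does surgery fail the screen at the planned rates?** With p̄ the pooled rate, SE₀ = √[p̄(1−p̄)(1/n₁+1/n₂)] and SE₁ = √[0.30·0.70/n₁ + 0.45·0.55/n₂], P(crude p < 0.10) ≈ Φ[(0.15 − 1.645·SE₀)/SE₁].

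- 78/118: p̄ = 0.390, SE₀ = 0.0712, SE₁ = 0.0692; Φ(0.475) = 0.683, so surgery fails in 32%.
- 100/120: p̄ = 0.382, SE₀ = 0.0658, SE₁ = 0.0645; Φ(0.648) = 0.741, so surgery fails in 26%.

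This step needs no assumption about confounding.

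**Step 2. How far can the crude contrast move?** Assume one binary severity factor with odds ratio 4 for death and 30% mortality in non-severe conservative patients. Odds 0.4286 × 4 = 1.714 give 63.2% in severe patients. With no surgery effect and a severe share of 30% operated versus 60% conservative:

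- operated: 0.7·0.30 + 0.3·0.632 = 0.399
- conservative: 0.4·0.30 + 0.6·0.632 = 0.499
- crude OR 0.67, although the true OR is 1

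With a true conditional OR of 0.524, the crude OR is 0.37–0.43 when conservative patients are sicker (severe share 30% or 40% operated versus 60%). It is 0.73–0.84 when operated patients are sicker (60% versus 40% or 30%).

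**Step 3. Simulated cohorts of 220.** The one-factor rows use the severity factor of step 2, 100/120 patients and 2,000 cohorts each. The six-factor rows use standardised confounders: mild is 0.15 log-odds per SD on surgery and 0.2–0.4 on death; moderate is 0.2–0.3 and 0.3–0.6. Ranges cover separate runs with similar settings.

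| Scenario (assumed) | Crude test p < 0.05 | Treatment and confounders forced in | Surgery fails p < 0.10 |
|---|---|---|---|
| No effect, one factor, 40% vs 60% severe (either way) | 17–18% | 5% | 73–74% |
| No effect, one factor, 30% vs 60% (either way) | 31–33% | 5% | 54–56% |
| No effect, six mild factors, same direction | 12–14% | 6% | – |
| No effect, six moderate factors, same direction | 36–47% | 5% | – |
| No effect, six mild factors, alternating signs | 5% | – | – |
| OR 0.524, one factor, balanced | 56% | 59% | 33% |
| OR 0.524, operated sicker, 60% vs 40% | 21% | 55% | 69% |
| OR 0.524, operated sicker, 60% vs 30% | 9% | 54% | 85% |
| OR 0.524, operated sicker, six factors | 6–24% | 50–57% | 65–88% |
| OR 0.524, conservative sicker, one factor | 86–94% | 54–59% | 3–8% |

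The 86–94% in the last row is not genuine power, because the crude odds ratio overstates the benefit.

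**Step 4. The screened regression itself.** Under no effect, with surgery counted only if its crude p < 0.10, it rejected in 4.6% (mild) and 4.2% (moderate) of six-factor cohorts, and in 2.8–3.5% of the confounded one-factor cohorts (severity forced in). With surgery forced in and only the covariates screened, the six-factor rates were 6.3% and 5.9%. Its cost is power: with operated patients sicker, surgery was significant after the screen in 31% (60% vs 40%) and 15% (60% vs 30%), against 55% and 54% with no screen. A confounder worth 0.3 log-odds per SD passed the screen only about 50–60% of the time.

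**The case against.** Three points on the other side have force.

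- **The wording is generic.** One sentence lists tests for every kind of variable. It never says that χ² is the primary or only test for mortality, and it does not say whether treatment is screened as a candidate or kept as the exposure. A reader might infer that the plan commits to a crude χ² as its primary analysis and will discard surgery; the article does not state either. What stands is that every comparison test listed is unadjusted, and that no sentence makes the regression the estimate of the surgery effect or protects the treatment term.
- **Type I error.** A reader might infer that the whole planned analysis inflates false positives. Step 4 does not support that: the screened regression stayed at about 3–5% under no effect. The inflation belongs to the crude test.
- **The sizes are assumed.** The article gives no severity distribution by arm. Confounders that offset each other left the crude test at 5%, and surgery is rarely screened out (3–8%) when conservative patients are sicker. The OR of 0.524 comes from the sponsor's crude unpublished data and may not be the true conditional effect.

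A full analysis plan might name confounders. That would excuse silence, but the article states a p-value entry rule, and a plan that kept treatment and confounders in regardless of p would have to depart from it.

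**Conclusion.** The point holds as a badly fixed method. Followed literally, the plan gives a crude comparison open to confounding by indication and no assured adjusted estimate for its primary question.

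The firmest figure is the 26–32% chance that surgery misses the screen at the protocol's own rates. It rests only on those rates, the stated group sizes and the literal reading that treatment is screened.

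The rest is conditional on confounding in one direction, of assumed strength: crude rejection of a true null in roughly 12–47% of cohorts, or crude power of roughly 6–24% against 50–57% with forced adjustment when sicker patients are operated on. These figures show what can happen; they do not predict this cohort, and the direction is unknown.

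**What to change.** State that the primary mortality result is an adjusted surgery effect. Keep treatment in the model regardless of p, with a short fixed list measured before the treatment decision: age, GCS, haematoma volume, supra- or infratentorial site, intraventricular blood or midline shift, antiplatelet regimen and centre. Overlap or inverse-probability weighting on the same list is an alternative. Expected deaths are 100 × 0.30 + 120 × 0.45 = 84, so the list should stay short.

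For PIB in operated patients on versus not on LOAPT, expected events are 100 × 0.23 + 180 × 0.10 = 41. Weight on the same list without antiplatelet regimen: regimen exists only in patients on LOAPT, so it determines the exposure and would leave no overlap.

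Keep χ² as descriptive and the p < 0.10 screen for exploratory risk-factor work only. Fix this before outcomes are analysed.

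The cost is revised wording, modest analysis work and possibly a slightly wider interval. Most of the variables are eligibility criteria in Table 1 or fall in the domains under Data collection, and regimen types appear under Study definition. Table 4 is not legible here, so the sponsor should confirm that each item is recorded before treatment.

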### Data collection

In case the patients meet our criteria, all information, including the demography, clinical information, preoperative radiological data, intraoperative findings, and laboratory and TEG data, will be recorded on the case report form (CRF). After being discharged, all the patients were followed up on a regular basis by outpatient visit and on telephone 3 months and 6 months after primary hemorrhage, respectively. During each follow-up visit, the survival condition, mRS, ACCE, and medication will be recorded. If the patients feel unable to undergo radiological examination in the participating center, a follow-up cranial image will be required. Once radiological examination is completed, the patients’ imaging data will be transmitted to the Tiantan hospital (this center will work as an imaging interpretation center) to reconfirm several events, including SSICH, PIB, and postoperative ischemic disease. During the study, the researchers are required to protect privacy for the patients and ensure the confidentiality of their medical information. The information collection schedule is presented in Table 4.

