The last focus of this study is ischemic complication after discontinuing antiplatelet medication. It is worth mentioning that the patients on antiplatelet medication are put at high risk of developing ischemic diseases including cardiovascular diseases and ischemic stroke. After a long period of discontinuing antiplatelet treatment, just for surgery, it is possible for these patients to develop ischemic diseases perioperatively or postoperatively [27]. This risk may be significantly higher for patients with ischemic stroke as neurosurgery could affect the cerebral blood flow and perfusion [2]. After the treatment of spontaneous intracranial hemorrhage, it is advisable to resume antiplatelet treatment. However, what confuses neurosurgeons is when and how to safely re-start antiplatelet medication. Moreover, there is currently still no relevant study reporting the incidence and risk factors of ACCE after neurosurgery in SSICH patients on LOAPT. Thus, credible evidence is needed to guide postoperative management. In this study, the patients will be followed up until 6 months after primary hemorrhage to investigate the risk of ACCE and the association between the discontinuation of antiplatelet treatment and ischemic complications. It is believed that this study will also provide an evidence to prevent SSICH patients on LOAPT from the development of ischemic complications and a basis for further investigation into the safe resumption of antiplatelet treatment in the future.

Based on our current study design, however, there remain some questions left unresolved. The first one is the indications of neurosurgery for SSICH patients on LOAPT. The second one is the effect of craniotomy, endoscopy, and minimally invasive surgery on SSICH patients on LOAPT. The third one is the advantage of different tools in assessing platelet function. The fourth one is when and how to resume antiplatelet treatment after neurosurgery. Surgical outcome and safety tend to be what neurosurgeons focus on. Despite the limitations to which our current study is subject, it is still believed that our study could provide a basis for the further exploration of appropriate treatment strategy for spontaneous intracranial hemorrhage patients on LOAPT.

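### Choosing independent risk factors by a univariate p < 0.10 screen, then reporting ordinary ORs and 95% CIs, carries a substantial chance of false factors and exaggerated ORs

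*Protocol article*

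**What the plan says.** The statistical paragraph of the Results section describes a two-step search for independent risk factors. Factors with p below 0.10 "in univariate analysis were entered into a multivariate logistic regression model. The result was indicated as odd ratio (OR) and 95% confident interval (CI". A p "value of < 0.05 was treated as statistically significant". No adjustment for the selection step is mentioned.

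The sentence names neither the outcome nor the population of the model. The nearest stated aim is the third one in the same paragraph, an analysis announced in these words (final verb omitted): "in order to investigate the intra/postoperative complications and the risk of ischemic disease after discontinuing antiplatelet treatment, the characteristics of SSICH patients on LOAPT will". The Discussion adds, for adverse cardiovascular/cerebral events (ACCE), that "there is currently still no relevant study reporting the incidence and risk factors of ACCE after neurosurgery in SSICH patients on LOAPT".

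For PIB, the sample-size paragraph gives an expected count, in the calculation for the coagulation assessment system: "92 operated SSICH patients on LOAPT, PIB group: *n* = 23; non-PIB group: *n* = 69". No ACCE rate or count is given. The data collected are broad: demographic, clinical and radiological data, "intraoperative findings, and laboratory and TEG data, will be recorded on the case report form (CRF".

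**The concern.** A factor is reported because it looked strong in the same data that are then used to estimate its effect. Three consequences follow if nothing corrects for this:

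- Each unrelated factor has a chance to be called an independent risk factor, and these chances add up over the candidates.
- Real factors are reported mainly when chance has made them look larger, so their ORs are biased away from 1.
- The ordinary 95% CI does not have 95% coverage for factors that entered only because they passed the screen.

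The risk-factor results are meant to inform surgical risk assessment and management after surgery. A chance finding with a convincing OR and interval could be carried into both. This point is separate from confounding of the surgery comparison and from the AUC threshold.

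**Working it through.** **Event counts (Results, sample size).** PIB in operated patients on LOAPT: 0.23 × 100 = 23, and 0.23 × 92 = 21.2. The plan's 23 is reproduced at the target group size. Other outcomes to which the sentence could refer:

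- PIB in all operated patients: 23 + 0.10 × 180 = 23 + 18 = 41 events in 280.
- Deaths in patients on LOAPT: 0.30 × 100 + 0.45 × 120 = 30 + 54 = 84 events in 220.

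**Candidates.** No list or number is given, so 10, 20 and 30 are assumed. The range is plausible: the thrombelastography section alone names four routine coagulation tests and two platelet-inhibition rates, besides the other data domains.

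**Rough arithmetic.** With K unrelated candidates, 0.10 × K pass the screen on average, or 2 of 20. For one unrelated factor, half of the results with p < 0.10 also have p < 0.05. Its interval after passing therefore covers the truth about 1 − 0.05/0.10 = 50% of the time. Adjustment for other entered factors changes this, so the rule was simulated.

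**Simulation of the written rule, no factor truly related to the outcome.** Half the factors are binary and half continuous; those with univariate p < 0.10 enter a maximum-likelihood logistic model with Wald tests at 0.05.

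| Patients / events | Candidates | Correlation | At least one false factor | Coverage of entered factors |
|---|---|---|---|---|
| 92 / 23 | 10, 20, 30 | 0.2 | 30%, 45%, 54% | 66–72% |
| 100 / 23 | 10, 20, 30 | 0 | 35%, 57%, 70% | about 56% |
| 100 / 23 | 20 | 0.3 | 35% | 76% |
| 280 / 41 | 20 | 0 | 61% | 52% |
| 220 / 84 | 20 | 0.2 | 46% | – |
| 220 / 84 | 20 | 0 | 61% | 53% |

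More events do not remove the problem.

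**Exaggeration (100 patients, 23 events).** One true factor with OR 1.6 has a median reported OR of about 1.7 to 1.9 once it passes the screen, and about 2.0 to 2.1 when it is significant.

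**Interval width.** That same true factor, once selected, is covered 96–98% of the time. With three true factors of OR 1.6, coverage over all entered factors is 85%, 78% and 74% for 10, 20 and 30 independent candidates, but 96% for 20 candidates correlated at 0.3. Restoring 95% needs intervals about 1.2 to 1.4 times as wide on the log-OR scale, and no widening in the correlated case.

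**Which part of the remedy does what (23 events).**

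- Three candidates: about 11–13% of studies have a false factor, with or without the screen.
- Twenty candidates without the screen: 76%.
- Three prespecified factors, no screen: coverage about 96%.

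The short list lowers the false-claim rate. Dropping the screen restores coverage. Penalisation is not needed for either.

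**The case against.** The strongest reply is that the regression sentence names no outcome, population or candidate list. The 23 of 92 is the basis of an AUC calculation, not of a risk-factor model, and the case report form describes what is recorded, not what will be tested. An article may leave the candidate list to the full protocol or analysis plan. This stands: a reader might infer that any number of factors will be screened, but the documents do not say so, and a missing list is no fault here. What does not fall away is the screen itself, which is written into the article and would still apply to whatever list exists.

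Two further inferences also go too far. A reader might conclude that a false factor is likely. With mildly correlated candidates the chance passes one half only at about 30 of them, and with independent ones at about 20. A reader might also conclude that the intervals are far too narrow. The under-coverage comes mostly from selection of shifted estimates, and a true factor, once selected, is covered at about the nominal rate.

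It is also fair to say that risk-factor modelling belongs to a third, observational aim. The planned cohort comparisons of mortality and PIB do not depend on it.

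**Conclusion.** The point holds as a weakness in a stated method. If the rule is applied to PIB in operated patients on LOAPT, there is a substantial chance of at least one false factor: about 30–54% for 10 to 30 mildly correlated candidates with no true effect, and up to 70% if they are independent. ORs of selected real factors are exaggerated, and 95% CIs for noise factors that pass the screen cover about 56–76%.

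These sizes rest on assumed candidate numbers, correlations and effect sizes. The count of about 23 PIBs is the plan's own. It might be inferred that the small event count is the cause, but 84 events in 220 give much the same false-factor rate. The drivers are the data-driven selection and the number of candidates. No size is put on the ischaemic-event model, because the documents give no event rate; the same mechanism applies to it.

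**What to change.** In the statistical paragraph of the Results section, replace the p < 0.10 entry rule for the PIB and ischaemic-event risk-factor models:

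- Name the outcome and population of each model.
- Before outcome data are analysed, name a short list of clinically chosen baseline factors, sized to the events. For 23 PIBs this is about two to four (23/2 = 11.5 to 23/4 = 5.75 events per factor), and fewer if ischaemic events are fewer.
- Enter all of them without a p-value screen and report those ORs and CIs. Ordinary logistic regression suffices; Firth penalisation is optional where events are sparse.
- Report any other factor as exploratory, and do not call it an independent risk factor.
- If a screen is kept, repeat the whole selection within a bootstrap and report selection-corrected estimates.

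The cost is a change of wording and a little programming, with no new patients or data. Fewer factors can be claimed, and Firth or bootstrap fits may need software beyond the named SPSS version.
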